## Abstract

Supplemental Digital Content is available in the text

## Introduction

1

Obstructive Sleep Apnea-Hypopnea Syndrome (OSAHS) is a common, chronic sleep disease, which a person frequently apnea and hypoventilation during his or her sleep.^[1]^ This is due to the lack of exercise tension of the tongue and/or airway dilators during sleep, resulting in obstruction of the upper respiratory tract. Its clinical characteristics include snoring (irregular snoring), patients consciously hold their breath (even being repeatedly awakened), often accompanied by a series of symptoms such as increased nocturnal, morning headache, dizziness, or pharyngeal dryness.^[2]^ And clinical evidence also suggests that OSAHS may contribute to the development of systemic hypertension, cardiovascular disease, and abnormalities in glucose metabolism.^[3–5]^ Moreover, OSAHS is insidious, and patients are often unaware of its developments, which seriously threaten people's health. The prevalence of OSAHS male is estimated to be 3% to 7%, and for female 2% to 5% in USA.^[6]^ There is currently a lack of epidemiological statistics on the disease in China, and the prevalence is estimated to be higher than 4%. Obesity is considered as the main reason for the occurrence of OSAHS.^[7]^ With the increase in overweight and obese people, the incidence of the disease will continue to rise.

Early recognition and appropriate therapy are the primary options for managing the disease.^[8]^ The overnight polysomnogram is the standard diagnostic test for OSAHS.^[6]^ It can simultaneously record multiple physiological signals during sleep, such as electroencephalogram, electrooculogram, electromyogram, oronasal airflow, and oxyhemoglobin saturation. As a chronic disease, the treatment of OSAHS is mainly to relieve upper airway obstruction, and needs to education and follow up patients continuously, and adjust the treatment strategy in time to ensure the efficacy.^[9]^ Lifestyle modifications, such as weight loss, alcohol sedative-avoidance, smoking cessation, avoidance of sleep deprivation, will decrease both the symptoms of OSAHS and the comorbid conditions.^[7,10]^ In addition, Chinese medicine has also become an effective treatment for OSAHS.^[11,12]^ All in all, there have been an increasing number of clinical trials of OSAHS in recent years. However, like clinical trials in other fields,^[13–15]^ the clinical trials of OSAHS also have heterogeneous outcomes, surrogate outcomes, subjective outcomes, and composite outcomes, as well as lack of endpoints or patient perspectives.

The best method to improve the reporting of outcomes is to develop a core outcomes sets (COSs), that is, the minimum set of outcomes in which all studies in a particular situation are scientifically agreed and reported.^[16]^ The COSs must be measurable and relevant. Involving patients and other key stakeholders are the key to achieving relevance. Studies have shown that the COS can make the reporting of outcomes of the study more standardized.^[17,18]^ With the Core Outcome Measures in Effectiveness Trials (COMET) Initiative founded and committed to the development, implementation, dissemination and update of COSs by published the consensus-based standards for the selection of health measurement instruments (COSMIN), the development and implemented of COSs has become an inevitable trend.^[19]^

To date, there is currently no available COSs for OSAHS's clinical trials. The first aim of this study is to develop a COS for OSAHS's clinical trials. The second aim is to select a measurement instrument for each outcome included in the COSs with the method recommended by the COMET initiative after completing the COSs. Finally, we will focus on the promotion of this COSs.

## Methods

2

The development of this COS follows COMET and COS-standard for Development core outcomes sets -standard for developmerecommendations.^[19,20]^ At the same time make appropriate adjustments according to the actual situation. After completing the registration, there are 5 stages:

(1)set up a Steering Group, defining the scope of this COSs;(2)identifying potential core outcomes by systematic review and semi-structured interviews;(3)identifying final COSs by consensus process, includes Delphi survey and face-to-face meeting;(4)identification and evaluation of instruments used to measure the final COSs;(5)promotion and updates. See detail in Figure 1.

**Figure 1 F1:**
[figure not shown]
Flowchart of the study design.

### Prospective registrations

2.1

This study has been registered on the COMET database (Number: 1544). (http://www.comet-initiative.org/Studies/Details/1544)

### Steering Group

2.2

We plan to form a national Steering Group to support the development of this COSs. The Steering Group includes 3 expertis in the fields of OSAHS and 1 expert in COSs development. In addition, this study also included 3 fellows and identifies a leader among them, in line with core outcomes sets -standard for developme recommendations.^[20]^ Members of the Steering Group and fellows were contacted by email and telephone regarding key decisions.

### Scope of the core outcome set

2.3

The aim of this article is to present a protocol for a study to develop a COSs for clinical trials in the patients (≥18 years) with OSAHS. Gender and race of patients are not limited. We foresee that the COSs will be used in OSAHS clinical trials in various interventions.

### Identifying potential core outcomes

2.4

The potential core outcomes will be generated by extracting outcomes from the published literature on the OSAHS through a systematic review. In addition, a series of semi-structured interviews with individuals in OSAHS can complement the potential core outcomes.

#### Systematic review

2.4.1

##### Research question

2.4.1.1

What outcomes are reported in the medical literature for OSAHS?

##### Inclusion criteria and exclusion criteria

2.4.1.2

The inclusion and exclusion criteria for the literature are shown in Table 1.

**Table 1 T1:**
[figure not shown]
The inclusion and exclusion criteria of systematic review.

##### Search strategy

2.4.1.3

We plan to search the following databases: PubMed, Embase, Cochrane library, and Web of Science. A comprehensive search strategy will be used (See detail in Supplemental Digital Content (Appendix Table 1), Key terms used to guide the search will include “obstructive sleep apnea”, “upper airway resistance sleep apnea syndrome”, “OSAHS” and “randomized controlled trials”. Language restrictions will not be applied to the search strategy; however, selection of relevant articles will be restricted to English language publications.

##### Study selection

2.4.1.4

The initial selection of studies identified in the search will be conducted using predetermined review inclusion/exclusion criteria. Firstly, 2 reviewers will independently assess the titles and abstracts of selecting studies. Secondly, full texts of studies which meeting the inclusion criteria or uncertainty regarding inclusion of title/abstract screening will be retrieved and reviewed with final decisions by the same reviewers. The third independent reviewer will be consulted to resolve the disagreement.

##### Data extraction

2.4.1.5

Data will be extracted independently by 2 review authors and checked by a third author. Any unclear and/or unavailable data will be identified by contacting study authors. The following data will be extracted from each included study: author, year and journal of publication, intervention(s), each effectiveness outcome reported, whether the outcome was defined or not, the definition used, the indicators and/or tool(s) used to operationalism or measure the outcome, the time point or period of outcome measurement, and how the outcome was reported.

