##### Data analysis and presentation

2.4.1.6

Two reviewers will independently standardize the outcomes and categorize them into different domains. The following process will be followed:

(1)adjust the outcomes to standard terminology (If no relevant terminology, the Steering Group will be consulted.);(2)composite outcomes will be divided into a single outcome;(3)define duplicate outcomes will be deleted;(4)categorize outcomes into different domains (such as mortality, quality of life, treatment satisfaction and adverse event);(5)the frequency of each outcome and the number of outcomes in each domains will be counted;(6)reviewers will check and resolve the disagreement through discussion with the other reviewer;(7)the Steering Group will conduct a final review.

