#### Semi-structured interviews

2.4.2

Adult patients with OSAHS will be interviewed to obtain outcomes that the patient considers important. This study plans to interview 10 patients (men and women half), they must meet the following conditions:

(1)no communication disorders or mental illness;(2)medical history more than 3 years;(3)agree to be interviewed. By comparing the outcomes of the systematic review, the 2 reviewers will determine which outcomes are new. Whether it will be included in the potential core outcomes should be decided by the Steering Group.

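### The data extraction item is limited to effectiveness outcomes, which contradicts the open review question and the adverse-event domain, so the review would not systematically supply adverse-event outcomes

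*Protocol article*

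**What the plan says.** Four statements in the Protocol article describe what the systematic review is to collect.

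- Research question (2.4.1.1): "What outcomes are reported in the medical literature for OSAHS". There is no restriction by type of outcome.
- Section 2.4, on where candidates come from: "The potential core outcomes will be generated by extracting outcomes from the published literature on the OSAHS through a systematic review". Again there is no restriction.
- Data extraction (2.4.1.5): the listed outcome item is "each effectiveness outcome reported, whether the outcome was defined or not". The definition, instrument, time point and manner of reporting are then recorded for that same outcome. No item covers harms.
- Data analysis and presentation (2.4.1.6): the reviewers will "categorize outcomes into different domains (such as mortality, quality of life, treatment satisfaction and adverse event". They then count how often each outcome occurs and how many outcomes each domain holds.

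Outcomes can also enter outside the review. Section 2.4 says that "a series of semi-structured interviews with individuals in OSAHS can complement the potential core outcomes". Ten patients are to be interviewed, and for any new outcome they raise, "Whether it will be included in the potential core outcomes should be decided by the Steering Group" (2.4.2). The Steering Group reviews the categorised outcomes (2.4.1.6) and the preliminary list (2.5.1). Each Delphi participant may add two outcomes in round 1.

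**The concern.** The extraction list determines what reviewers take from each paper. If it names effectiveness outcomes only, an outcome that a trial reports as an adverse event falls outside it. The later step that classifies and counts adverse-event outcomes would then have no planned input.

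The review is the systematic source of the questionnaire that the Delphi panel rates. The set is meant for trials of various interventions in adults with OSAHS (2.3), so harms are natural candidates. If they are not extracted, their place in the core outcome set could depend on whether somebody thinks to suggest them, and not only on how the panel rates them.

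**Working it through.** The documents give no figure on this point and no formula applies. The check sets the sections side by side and follows an adverse-event outcome through the plan.

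**Step 1. Scope at each stage of the review**

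| Section | Scope of outcomes | Covers adverse events? |
|---|---|---|
| 2.4 Source of candidates | Outcomes in general | Yes |
| 2.4.1.1 Research question | Outcomes in general | Yes |
| 2.4.1.5 Data extraction | Effectiveness outcomes | Not as written |
| 2.4.1.6 Domains and counts | Named domains include adverse event | Yes, by name |

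The extraction item is the only narrow entry. It stands between a question and an analysis that are both wider, so the sections cannot all be followed literally.

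**Step 2. Which named domains are affected**

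Section 2.4.1.6 gives four examples of domains. Mortality, quality of life and treatment satisfaction can all be reported as effectiveness outcomes, so the extraction item does not shut them out. Adverse event is the one that cannot readily be filled from an extraction limited to effectiveness. The contradiction concerns that domain.

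**Step 3. Routes left open to an adverse-event outcome**

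- *Interviews (2.4.2).* There is no limit by type of outcome, but there are 10 patients, and a new outcome enters only if the Steering Group agrees.
- *Steering Group review (2.4.1.6 and 2.5.1).* The group has three OSAHS experts and one expert in core outcome sets. It could notice the gap, although the article does not say that it will add outcomes at these reviews.
- *Round 1 additions (2.5.1).* With the target of 180 participants and 2 additions each, the ceiling is 180 × 2 = 360 nominations. This is an upper limit, not an expected number, and nominations may overlap.

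Each route depends on someone volunteering the outcome. None replaces systematic extraction from the included trials.

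**Step 4. What happens to an outcome added in round 1**

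All outcomes go forward to round 2, so an added outcome is not lost at once. It was not on the round 1 questionnaire, however, so the whole panel scores it for the first time in round 2. Outcomes that miss the consensus rule in that round (more than 70% scoring critical and less than 15% scoring limited importance, by stakeholder group) are dropped. A listed outcome comes to that decision after a full round of scoring, with the panel's score distribution shown to participants. An added outcome comes to it with scores only from those who proposed it.

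**The case against.** The strongest reply is that *effectiveness* is loose wording. Three other statements describe an unrestricted review, one of them names an adverse-event domain, and the article contains other slips of language. Reviewers who work with that domain, with a third author checking the extraction, might well notice that it is empty. The extraction form and Table 1 (inclusion and exclusion criteria) are not shown, so what reviewers would actually record is not known. This stands as far as intent goes: nothing shows a decision to exclude harms. It does not remove the contradiction, because the extraction list is what reviewers are told to follow and two of them could read it differently. The third author would also be checking against the same list.

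A reader might infer that safety outcomes can never enter the candidate list, or that none of those reported in the trials would reach it from the review. The documents do not support either. Interviews, Steering Group review and round 1 additions remain open, and up to 360 nominations is not a negligible route. Mortality can be extracted as an effectiveness outcome, so even under a literal reading the gap is secure only for outcomes reported as adverse events.

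**Conclusion.** Wrong as written. The extraction item in 2.4.1.5 contradicts the unrestricted question in 2.4.1.1 and the adverse-event domain in 2.4.1.6. Followed as it stands, it would keep adverse-event outcomes out of the systematic source of the Delphi list. They would then depend on interviews, Steering Group review or round 1 additions, which are open but weaker.

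The size cannot be expressed as a number, because the documents do not say how many adverse-event outcomes the included trials report. The conclusion assumes that the extraction list is applied literally. If reviewers read it loosely, the harm is smaller and consists of inconsistent extraction. It does not rest on any claim that the authors meant to leave harms out, or that the final set would lack a safety outcome.

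**What to change.** In 2.4.1.5, replace the restricted outcome item with *each outcome reported, including adverse events/harms*. Leave the remaining fields (definition, instrument, time point, manner of reporting) as they are, so that they apply to every outcome. This brings extraction into line with 2.4.1.1 and 2.4.1.6. No new domain is needed.

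The change should be made before extraction begins. The cost is then one phrase in the protocol and one more type of outcome to record from papers already being read. If extraction has already been done under the narrow wording, the included papers would have to be read again for adverse events.

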##### Data analysis and presentation

2.4.1.6

Two reviewers will independently standardize the outcomes and categorize them into different domains. The following process will be followed:

(1)adjust the outcomes to standard terminology (If no relevant terminology, the Steering Group will be consulted.);(2)composite outcomes will be divided into a single outcome;(3)define duplicate outcomes will be deleted;(4)categorize outcomes into different domains (such as mortality, quality of life, treatment satisfaction and adverse event);(5)the frequency of each outcome and the number of outcomes in each domains will be counted;(6)reviewers will check and resolve the disagreement through discussion with the other reviewer;(7)the Steering Group will conduct a final review.

#### Semi-structured interviews

2.4.2

Adult patients with OSAHS will be interviewed to obtain outcomes that the patient considers important. This study plans to interview 10 patients (men and women half), they must meet the following conditions:

(1)no communication disorders or mental illness;(2)medical history more than 3 years;(3)agree to be interviewed. By comparing the outcomes of the systematic review, the 2 reviewers will determine which outcomes are new. Whether it will be included in the potential core outcomes should be decided by the Steering Group.

### Determining core outcomes

2.5

Following the guidance of COMET, like other similar studies, this study will determine the final core outcomes through Delphi survey and face-to-face meeting.

#### Delphi survey

2.5.1

We will use a Delphi survey to develop consensus on the core outcomes from those identified in the systematic reviews and semi-structured interviews. The advantage of this technique over a roundtable meeting is that it avoids situations where some people can lead the discussion or situations where other individuals feel obligated to agree with the opinions of more senior members. In order to improve efficiency, the questionnaire will be completed online using appropriate online survey design software.^[21]^ A minimum of 3 Delphi rounds is planned. There is currently no standard sample size calculation method in the Delphi process, but our goal is a total of 180 participants, including at least 30 patients (Confirmed cases from tertiary hospitals aged over 18 with a history of more than 3 years.).^[22]^ We will strive to increase the response rate of the participants.

The participants are all stakeholders. In addition to patients, we plan to include the following 3 groups of people:

(1)clinicians: respiratory physician, cardiologist, otolaryngologist, general practitioner, doctor of traditional Chinese medicine, nurse;(2)researchers: experts in respiratory diseases at domestic and foreign medical schools, respiratory specialists in various research institutions;(3)policy-makers: national, provincial, municipal, county, and other levels of health management personnel, some health policy-makers outside of China will also be invited. Potential participants will determine whether they are willing to participate in the Delphi survey via email or phone.

A preliminary list of potential outcomes will be produced by reviewers, and will be reviewed by the Steering Group. Participants are asked to evaluate the importance of the listed items. Participants can also choose to add other items they think are missing and score each item added. The detailed process will proceed as following.

Round 1

In Delphi survey round 1, the first is to obtain the participant's name, email address and their location in order to provide every participant with a unique identifier. Secondly, participants will be asked to identify the stakeholder group. The questionnaires based on the preliminary list of potential outcomes will contain lay terminology alongside clinical terms to assist participants (especially patients) in understanding complex terminology. In the survey, the order of outcomes and the order of domains within outcomes will be randomized. The participants will be asked to rate the potential outcomes on a 9-point Likert-scale.^[23]^ Scores will be grouped into 1 to 3 (signifies an outcome is of limited importance), 4 to 6 (important but not critical), and 7 to 9 (critical). If a participant feels that they did not understand a certain outcome, they will be able to select unable to score. In addition, each participant is allowed to add 2 additional outcomes and add a score to each added outcome. The Delphi survey round 1 will be required to complete the questionnaire within 3 weeks. A reminder email will be sent on the second weekend. Non-responders will not be invited to participate in round 2.

Two reviewers will independently analyze and collate the responses from the first round. Any disagreements will be resolved through discussion or determined by the Steering Group. The responses of round 1 will be summarized using descriptive statistics, including the additional outcomes. For each outcome, the number of participants who have scored the outcome and the distribution of scores will be summarized by reviewers. All outcomes will be carried forward to round 2. In addition, participants in the round 2 can also see the distribution of score of each outcome.

Round 2

The purpose of the round 2 will be enabled participants to reflect on their score based on the views of stakeholders on peers and score the outcomes again. As in round 1, participants will be asked to rate all outcomes again on the 9-point Likert-scale. This round 2 will also be required for completion within 3 weeks. Participants will be reminded by email on the weekend of the second week.

If an outcome scored “critical” by more than 70% of participants from any stakeholder group and “limited importance” by less than 15% of participants from any stakeholder group (See detail in Table 2), it will be carried forward for further consideration in round 3. Like the previous study, the theoretical basis for this study to do so is that for an outcome to be included in COS, it requires agreement by the majority regarding the critical importance of the outcome, with only a small minority considering it to have little importance.^[24]^ The purpose of this round of the Delphi survey is to determine the most important outcomes, and all other outcomes will be discarded. As in the previous round, 2 reviewers will independently conduct statistics and analysis. Any disagreements will be resolved through discussion or determined by the Steering Group.

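### Outcomes added in round 1 go into round 2 with only their proposers' scores as feedback, and can be discarded after a single panel rating

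*Protocol article*

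**What the plan says.** All of the relevant rules are in section 2.5.1 of the Protocol article.

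- **What is scored in round 1.** The survey instrument is built from the preliminary list: "The questionnaires based on the preliminary list of potential outcomes will contain lay terminology alongside clinical terms". In addition, "each participant is allowed to add 2 additional outcomes and add a score to each added outcome".
- **What is summarised and carried on.** "The responses of round 1 will be summarized using descriptive statistics, including the additional outcomes", and "All outcomes will be carried forward to round 2".
- **What is shown in round 2.** "participants in the round 2 can also see the distribution of score of each outcome". Nothing excepts the additions.
- **What round 2 asks.** Its purpose is reflection and re-scoring: "participants will be asked to rate all outcomes again on the 9-point Likert-scale".
- **What happens at the end of round 2.** An outcome is retained on a two-part rule that begins "If an outcome scored “critical” by more than 70% of participants from any stakeholder group" and also requires fewer than 15% scoring it of limited importance. For everything else, "all other outcomes will be discarded".
- **What enters round 3.** Only the outcomes retained after round 2.

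The panel target is 180, with at least 30 patients, and at least three rounds are planned.

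**The concern.** These rules suit an outcome that was on the list from the start. They fit poorly for one that a participant adds in round 1, for two separate reasons.

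First, the score distribution shown beside the item in round 2 is not the panel's opinion. It is the rating of the person or few people who thought the item important enough to propose. Section 2.5.1 prefers a Delphi survey to a roundtable because it stops some individuals from leading the discussion. Showing an advocate's own score as the group distribution brings some of that influence back.

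Second, everyone except the proposer meets the item for the first time in round 2. They have no earlier score to reconsider, yet the discard rule applies at the end of that same round.

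Additions are also one of only two routes by which outcomes raised by patients can reach the list. The other is 10 interviews (section 2.4.2), after which the Steering Group decides whether a new outcome enters.

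**Working it through.** The article states no figure that could be reproduced here, and no hypothesis test is involved. The check traces the sequence of ratings and counts them.

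**Inputs, all from section 2.5.1:** target panel 180; at most 2 additions per participant; retention at more than 70% critical and less than 15% limited importance, first applied after round 2; at least 3 rounds.

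**Step 1. Sequence of ratings.**

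| Stage | Listed outcome | Added outcome |
|---|---|---|
| Round 1 | rated by the panel | rated by its proposer(s) only |
| Feedback in round 2 | panel distribution, up to 180 raters | proposers' scores, as few as 1 rater |
| Round 2 | second panel rating | first panel rating |
| Panel ratings before the discard | 2 | 1 |
| Cycles of panel feedback before the discard | 1 | 0 |
| Panel ratings by the end of round 3, if retained | 3 | 2 |

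**Step 2. Base of the feedback.** Share of the planned panel behind the displayed distribution = k / 180, where k is the number of proposers.
- k = 1: 1/180 = 0.6%
- k = 5: 5/180 = 2.8%
- listed outcome with full response: 180/180 = 100%

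The ceiling on additions is 180 × 2 = 360, before duplicates are merged. It bounds the workload and says nothing about bias.

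**Step 3. How little such feedback could tell the panel (illustration, assumed inputs).** Suppose 60% of the panel would score the item critical, and proposers were a random draw from the panel. The standard error of the displayed share is √(0.6 × 0.4 / n):
- n = 1: 0.49
- n = 5: 0.22
- n = 180: 0.04

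Proposers are self-selected, so there may also be a shift. Suppose they score their own item critical 80% to 100% of the time, and the panel would do so 40% to 60% of the time. The displayed share is then too high by between 80 − 60 = 20 and 100 − 40 = 60 percentage points. None of these shares comes from the article; they show a plausible range only.

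**The case against.** The strongest reply is that later steps limit the harm.

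- An addition kept because its displayed score was high is rated again in round 3 with panel feedback, and then goes to the face-to-face meeting, where remaining disagreement is put to a vote at 70% (section 2.5.2). This stands: upward anchoring in round 2 cannot by itself put an item into the core outcome set. It does nothing for an item already discarded.
- The study's reviewers count how many participants scored each outcome. A distribution based on one person might therefore be recognised for what it is. This stands only in part: the round-3 text says that participants see that number, while the round-2 text promises only the distribution.
- Read literally, the critical-score part of the rule can be met by one stakeholder group, so an item that patients value is not necessarily outvoted. This softens the second limb, but the item still gets only one panel rating.
- The plan for at least three rounds leaves room for another. No extra round is assigned to additions, however, and the discard is fixed at the end of round 2.
- The two effects pull in opposite directions: a high displayed score favours retention, while a single rating risks loss. No net direction can be claimed.

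Three stronger readings are tempting but unsupported. A reader might infer that feedback is pooled over all participants, so that the professional groups swamp the patients. The article does not say whether the display is pooled or split by stakeholder group, and a condensed article may leave that format to the full protocol. A reader might also infer that proposers' round-1 scores count towards consensus. They do not: the criterion is applied only to round-2 and round-3 scores. Finally, a reader might take it as established that proposers' scores are uniformly high. That is likely, but the article gives no data on it.

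**Conclusion.** The point holds as a limited design flaw that follows from how the stated rules combine. Added outcomes are shown with feedback from self-selected raters, as few as 1 of a planned 180, and face the discard rule after one panel rating where listed outcomes have had two. If several participants propose the same item, their scores may be merged, but the raters are still those who proposed it.

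The lasting loss is confined to additions dropped after round 2, because those kept in error are examined again. The size of any bias in the feedback cannot be derived from the article, and its upward direction is an inference about how proposers score. The conclusion assumes that the feedback and discard sentences mean what they say for all outcomes, since no exception for additions is stated.

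**What to change.** Two changes to section 2.5.1, the first being the essential one:

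1. In round 2, present added outcomes as newly suggested and not yet rated by the panel, and leave out their proposers' scores. This costs one sentence and a survey setting. No change to the consensus tallies is needed.
2. Preferably, after the study's reviewers have merged duplicates, carry all added outcomes to round 3 with their round-2 panel distribution, and apply the retention criterion to them only after round 3. Each would then have two panel ratings and one cycle of panel feedback before it could be dropped, as listed outcomes already do.

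The second change makes the round-3 list longer, by an amount that depends on how many distinct additions remain after de-duplication. It also means that round 2 no longer filters these items. If that burden is judged too great, the first change is still worth making alone.
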